#### Twelve months follow-up

A re-interview of participants from both study arms done by telephone by the same interviewer will be performed after one year focusing on headache diagnosis, use of medication, and present burden of headache (number of headache days and intensity of headache). Headache associated quality of life will be assessed with MIDAS and HIT-6. SDS will be measured.

### Outcome measures

Outcome measures are listed in Table 
3. Primary outcomes are headache days and medication days per month comparing the two arms and change compared to baseline. With a simple, non-medication intervention as the present, any significant improvement in these parameters is judged to be of relevance. Proportions fulfilling commonly used clinical definitions of chronic headache (≥15 days/month) and medication overuse 
[75-78] at follow up are also clinically relevant and included as secondary outcomes. In addition, since clinically relevant outcomes in medication studies have been suggested to be 25 to 50% improvement in headache days and headache index, these are also included as secondary outcomes. 

**Table 3 T3:** Outcome measures and time points for application of the various outcomes (statistical calculations are further described in the Statistics section)

	**3 months**	**12 months**

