**Methods/Design:**

A double-blinded cluster randomised parallel controlled trial (RCT) of BI vs. business as usual. Intervention will be performed in primary care by GPs trained in BI. Patients with MOH will be identified through a simple screening questionnaire sent to patients on the GPs lists. The BI method involves an approach for identifying patients with high likelihood of MOH using simple questions about headache frequency and the SDS score. Feedback is given to the individual patient on his/her score and consequences this might have regarding the individual risk of medication overuse contributing to their headache. Finally, advice is given regarding measures to be taken, how the patient should proceed and the possible gains for the patient. The participating patients complete a headache diary and receive a clinical interview and neurological examination by a GP experienced in headache diagnostics three months after the intervention. Primary outcomes are number of headache days and number of medication days per month at 3 months. Secondary outcomes include proportions with 25 and 50% improvement at 3 months and maintenance of improvement and quality of life after 12 months.

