#### Patients

A short validated screening questionnaire for headache 
[80,81] including questions about headache frequency, intensity (as recorded on a visual analogue scale (VAS) 
[82]), presence of migraine and medication use will be mailed to all 18–50 year old patients on participating GPs’ patient lists. Names and addresses will be extracted from GP lists using a specially designed software (Mediata Ltd, Tønsberg, Norway). One written reminder will be sent to non-responding patients.

All patients with 15 or more days with self-reported headache per month and headache medication utilization on 10 days or more per month will be invited to participate.

Patients unable to participate in an interview in Norwegian will be excluded.

Baseline patient information (screening questionnaire and headache diary) will be collected by the Akershus University hospital research administration unit before any study-related contact between patient and their GP.

To avoid unblinding and carry-over of information from the BI to BAU, both GPs and patients will initially only receive basic information that this study aims to evaluate headache and headache care in primary care.

After the intervention part, all follow-ups will be conducted by the first author ([name]), who will be blinded in relation to which treatment the participant has received. All participating patients will receive a semi-structured interview and clinical and neurological examination.

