**Primary outcomes**		
Difference between BI and BAU in:		
a) number of headache days per month	X	
b) number of headache medication days per month	X	
Change relative to baseline in		
a) number of headache days per month	X	
b) number of headache medication days per month	X	

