**Secondary outcomes**		
Difference between BI and BAU in proportion of cases without chronic headache and without medication overuse	X	
Change relative to baseline in proportion of patients with more than		
a) 25% reduction of headache days	X	X
b) 50% reduction of headache days	X	X
Change relative to baseline in headache index (Area under curve for headache intensity versus time)	X	X
Change relative to baseline in		
a) headache days from headache diary	X	X
b) medication days from diary	X	X
Change relative to baseline in average headache intensity recorded by VAS (from headache diary)	X	X
Change relative to 3 month follow-up in self-reported health related costs		X
Change relative to 3 month follow-up in quality of life recorded as SF-36 and MIDAS/HIT-6		X
Change relative to baseline in:		
a) number of headache days per month		X
b) number of headache medication days per month		X
Relapse rate compared with status at 3 month		X

*Abbreviations: BI* brief intervention, *BAU* business as usual, *VAS* visual analogue scale, *SF-36* short form-36, *MIDAS* migraine disability assessment score, *HIT-6* headache impact test-6.

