[80,81]. However, especially among those with chronic or co-occurring headache types, diagnosing headaches is not always easy. The gold standard for making a specific headache diagnosis is an interview combined with a physical and neurological examination by a physician experienced in headache diagnostics. All patients will be diagnosed based on interviews by a GP trained and experienced in headache diagnostics also in order to avoid inter-observer variation ([name]).

Some of our data will be based on retrospective self-reports and therefore open to recall bias, although here is no reason to suspect systematic bias. In order to counteract this, we will also use headache data from prospective headache diaries 
[87]. Recent studies using a similar headache diary with written instructions before first consultation found high usefulness, acceptability and comprehensibility of the diary as well as good compliance and completeness of data 
[105,106]. We will use the headache diary for periods of two weeks. This period may seem too short for infrequent forms of headache, but in our sample of chronic sufferers this should not be a problem. In addition, a longer headache registration period may reduce compliance and cause greater interference with the cohort.

A common finding in many brief intervention studies and RCTs on alcohol use, are small reductions in alcohol consumption at follow-up also in the control group 
[73,107]. Possible reasons for this may be motivational effects of screening, sensitization to screening/measurements/follow-up, non-intended advice also in BAU group, and “regression towards the mean”. In this study we have tried to minimize most assessment effects by doing a double-blinded parallel RCT, and the screening questionnaire about medication use for headache is embedded with other questions about headache in the very short screening questionnaire. The control group will not receive the SDS screening before the three months follow-up and will therefore not be affected by this.

The SDS has not been validated against other measurements of dependency in MOH sufferers and, indeed, there is still much discussion as to whether MOH represents dependency 
[50-55,57]. Being fully aware of this, we will use the SDS score, not as an attempt to define dependency, but rather to distinguish between chronic headache subjects with and without medication overuse 
[30,35].

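### Table 3 makes uncontrolled change from baseline a primary outcome beside the BI-BAU differences, so a fall that owes nothing to BI could be reported as a primary result

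*Protocol article*

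**What the plan says.** Under Outcome measures, the article states: "Primary outcomes are headache days and medication days per month comparing the two arms and change compared to baseline". Taken alone, that sentence could mean change compared between arms. Table 3 separates the two ideas. One primary block is headed "Difference between BI and BAU in" and a second is headed "Change relative to baseline in". Each lists headache days and medication days per month at 3 months, and the second names no comparison of arms.

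Other parts of the article describe a smaller primary set:

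- The abstract says "Primary outcomes are number of headache days and number of medication days per month at 3 months" and does not mention change.
- Methods/Design states a comparative hypothesis, that BI is superior to BAU.
- The Statistics section counts two primary outcomes, describes a mixed linear model for BI-BAU differences, and applies a Bonferroni correction without giving the divisor.

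Three further statements bear on the point:

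- The invitation criterion is "All patients with 15 or more days with self-reported headache per month and headache medication utilization on 10 days or more per month", that is, thresholds on the two primary variables.
- The Discussion reports that control groups in comparable alcohol trials also improve. It offers as reasons "motivational effects of screening, sensitization to screening/measurements/follow-up, non-intended advice also in BAU group" and, next in the list, regression to the mean.
- Of headache days and medication days, Outcome measures says that "any significant improvement in these parameters is judged to be of relevance".

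Under Ethics and data security, the possible cross-over of the BAU arm depends on whether the main outcomes at three months show a significant benefit of BI.

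**The concern.** A change from baseline without a control mixes any effect of BI with everything else that moves over three months. Here the entry rule alone produces movement. People invited because they reported many headache and medication days will, on average, report fewer later, in both arms. The Discussion says as much about control groups.

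If the second block of Table 3 is a primary outcome in its own right, a significant fall in the BI arm could be presented as a primary success even when the BAU arm fell equally. The statement that any significant improvement is relevant does not prevent this. The cross-over condition refers to the main outcomes, so it inherits the same ambiguity.

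There is also a plain inconsistency of count. With four primary lines in one place and two in others, the Bonferroni divisor is undetermined.

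**Working it through.** **1. Primary lines counted by section.** Abstract: two variables at 3 months. Statistics: two primary outcomes. Table 3: two arm differences plus two changes from baseline, so four lines. The passages do not agree.

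**2. The planned size.** Power calculations gives 18 patients per arm unadjusted, 8 patients per GP, an ICC of 0.5 and 160 patients. Design effect = 1 + (8 − 1) × 0.5 = 4.5. Then 2 × 18 × 4.5 = 162, against 160 stated. The article does not show this step, but the figure is reproduced. At 160 patients the effective size is 80 / 4.5 = 17.8 per arm. The difference and SD behind the 18 are not given; 18 per arm at 80% power and two-sided 5% implies a standardised difference of about 0.93.

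**3. Expected fall without treatment (assumed inputs).** Regression to the mean = (1 − r) × excess, where the excess is measured over the mean of the source population and r is the correlation between the two occasions. For an excess of 6 to 8 days and r of 0.8 to 0.6, the fall runs from 6 × 0.2 = 1.2 to 8 × 0.4 = 3.2 days per month. A simulation with no treatment effect gave mean falls of about 0.7 to 6.2 days. It applied the article's two thresholds to normal scores limited to 0-30 days, with source means of 5-18 (headache) and 6-12 (medication), SD 6-8 and r 0.5-0.85.

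**4. How often such a fall is significant within one arm.** Take a fall of 2 days, an SD of change of 5 and 80 patients.

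- Independent patients: SE = 5/√80 = 0.559 and 2/0.559 = 3.58. Φ(3.58 − 1.96) = 95% at alpha 0.05.
- Design effect 4.5: SE = 0.559 × √4.5 = 1.186 and 2/1.186 = 1.69.
  - alpha 0.05: Φ(1.69 − 1.96) = 39%
  - alpha 0.025 (Bonferroni over two): Φ(1.69 − 2.24) = 29%
  - alpha 0.0125 (Bonferroni over four): Φ(1.69 − 2.50) = 21%

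In the simulation, with independent patients and alpha 0.025, the within-arm test was positive in 24% to 100% of trials at 80 per arm. At 18 per arm, close to the effective size in step 2, it was positive in 7% to 99%.

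**5. The same question for the arm difference.** In the same no-effect simulation, the BI-BAU test at alpha 0.025 was positive in about 2-3% of trials, with or without baseline adjustment. Randomised arms regress alike.

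**6. Cost of the unclear count.** At a standardised difference of 0.93 and 17.8 effective patients per arm, 0.934 × √(17.8/2) = 2.78. Power of the arm contrast is Φ(2.78 − 2.24) = 71% with two primary tests and Φ(2.78 − 2.50) = 61% with four.

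**7. What baseline adjustment adds (r assumed).** Residual variance is multiplied by 1 − r², so 2.78 is divided by √(1 − r²). For r = 0.3, 0.5 and 0.7 this gives 2.92, 3.21 and 3.90. Power at 160 patients is then 83%, 90% and 97% at alpha 0.05, against 80% unadjusted. At alpha 0.025 it is 75%, 83% and 95%, against 71%. This takes the design effect as unchanged by adjustment.

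**The case against.** The strongest reply is that nothing in the article says a within-arm change will be tested as proof that BI works. The hypothesis is comparative, the only model described is for BI-BAU differences, and no test of change alone is set out. The remark on any significant improvement can be read as declining to set a minimum relevant effect. The design also meets regression to the mean with a parallel control arm, and Population controls adds a chronic headache group without overuse to follow the natural course. All of this stands and makes misuse less likely. It does not remove the second primary block, which is printed apart from the arm differences and never tied to a comparison.

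A reader might infer more than the article supports:

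- **That the BI-BAU difference is itself distorted by regression to the mean.** It is not (step 5). Baseline adjustment is a matter of precision and of protection against chance imbalance.
- **That the arm differences are fixed as raw 3-month values.** Table 3 does not say so, and the covariates may be in the full protocol or analysis plan.
- **That the primary change compares a mailed questionnaire with an interview.** Diary days are listed separately as secondary, which suggests it, but Table 3 names no instrument for the primary lines. Any such mismatch would be shared by both arms. Moving to the diary would also change the endpoint.
- **That the false-positive rate within an arm is 95%.** That figure ignores both clustering and the Bonferroni correction.

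The responder rows in Table 3 ("Change relative to baseline in proportion of patients with more than") may be only awkward shorthand, since a 25% or 50% reduction is by nature relative to baseline. They still name no arm contrast.

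**Conclusion.** The point holds as a defect in the definition of the primary outcomes. Table 3 gives primary status to two uncontrolled changes and disagrees with the abstract, the hypothesis and the Statistics section. A valid randomised contrast already exists among the primary lines, so the trial's central comparison is sound. What is at risk is which result may be called primary, and hence what the cross-over condition refers to.

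The direction of the problem follows from threshold entry; its size does not follow from the article. The 2-day drift, the SD of 5, the correlations and the source distributions are assumptions. The design effect of 4.5 uses the article's worst-case ICC, which it does not state for change scores. On those inputs the chance of a significant within-arm fall with no effect of BI is 21% to 39% under clustering, and it can be far higher or lower under other inputs. The more certain cost is the undetermined divisor: 71% against 61% power for the arm contrast, on the article's own planning figures.

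**What to change.** 1. Make the only primary analyses the two BI-BAU differences at 3 months, in headache days and in medication days. Estimate them from the planned mixed model with the baseline value of the same variable as covariate.
2. Report within-arm change from baseline as descriptive, without a claim of effect.
3. Word the 25% and 50% responder rows as differences between BI and BAU.
4. Align Outcome measures and Table 3 with the abstract, the hypothesis and the Statistics section, and state that the Bonferroni correction for the primary outcomes covers two tests.
5. Reconcile the reference to main outcomes under Ethics and data security with the revised list.

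No switch of the primary instrument to the diary is needed. The cost is an edit to Table 3 and the sentences around it. Baseline data are already collected, and no patients or visits are added. The covariate also guards against chance imbalance: whole CME groups are randomised, typically of four to ten GPs, so if whole groups join, 20 GPs amount to between two (20/10) and five (20/4) groups. The downside is that the two before-after results lose primary status.

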**Primary outcomes**		
Difference between BI and BAU in:		
a) number of headache days per month	X	
b) number of headache medication days per month	X	
Change relative to baseline in		
a) number of headache days per month	X	
b) number of headache medication days per month	X	
**Secondary outcomes**		
Difference between BI and BAU in proportion of cases without chronic headache and without medication overuse	X	
Change relative to baseline in proportion of patients with more than		
a) 25% reduction of headache days	X	X
b) 50% reduction of headache days	X	X
Change relative to baseline in headache index (Area under curve for headache intensity versus time)	X	X
Change relative to baseline in		
a) headache days from headache diary	X	X
b) medication days from diary	X	X
Change relative to baseline in average headache intensity recorded by VAS (from headache diary)	X	X
Change relative to 3 month follow-up in self-reported health related costs		X
Change relative to 3 month follow-up in quality of life recorded as SF-36 and MIDAS/HIT-6		X
Change relative to baseline in:		
a) number of headache days per month		X
b) number of headache medication days per month		X
Relapse rate compared with status at 3 month		X

*Abbreviations: BI* brief intervention, *BAU* business as usual, *VAS* visual analogue scale, *SF-36* short form-36, *MIDAS* migraine disability assessment score, *HIT-6* headache impact test-6.

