[25,26,31,38], but is often complicated by temporary withdrawal symptoms such as worsening of headache, nausea, vomiting, hypotension, tachycardia, sleep disturbances, restlessness, anxiety and nervousness which typically occur 2–10 days after detoxification 
[26,27,40,41]. There is no established optimal withdrawal method for MOH though many different strategies have been suggested 
[25,36,37,39]. These include use of antiemetics and/or neuroleptics to reduce abstinence-like symptoms, intravenous administration of ergotamines and substitution of the offending painkiller with another. Steroid treatment has also been used to alleviate withdrawal reactions though this strategy is controversal 
[36,37,41-43].

Regarding prophylactic headache medication, there is also an ongoing discussion whether this should be initiated immediately at withdrawal or after completed withdrawal therapy 
[36,44].

Follow-up studies of various duration have reported relapse rates between 20–60% and findings from these studies suggest that patients have the highest risk of relapse within the first year after withdrawal 
[37,45-49].

MOH is a heterogenous disorder which has been suggested to include both subgroups with simple medication overuse as well as more complex detoxification-resistant cases 
[36,50-52]. Some of these cases may be more “dependency-like” and it has indeed been suggested that MOH shares some common neurobiological pathways with drug dependence and that MOH therefore may represents a kind of addictive behaviour 
[53]. Whether this applies to all MOH cases or specific subgroups defined by this particular “dependency-like” behaviour (eg. “complex” MOH) remains to be demonstrated. Two studies have demonstrated that most MOH patients fulfill criteria for dependency according to the Diagnostic and Statistical Manual of Mental Disorders, fourth edition (DSM-IV) 
[54-56]. Another study found that the dependency score based on the Leeds Dependency Questionnaire was similarly increased in MOH patients and illegal drug addicts 
[57].

Over the past decades several dependency assessment scales have been developed. The Severity of Dependence Scale (SDS) is a simple, validated scale which scores psychological dependence on a number of different substances 
[58-63]. Previous studies from our group have revealed that the SDS has both high sensitivity, specificity, positive and negative predictive values for detecting persons with MOH among chronic headache patients. 

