#### Headache classification

The headaches will be classified according to explicit diagnostic criteria of the ICHD-II and it‘s relevant revisions 
[83-86]. In this study we have defined chronic headache as 15 or more headache days per month for at least 3 months and/or 180 or more headache days per year as the ICHD-II does not provide an explicit definition for all headache diagnoses. The ICHD-II diagnosis will be made by the first author and by consensus in the project team based on the 3 month follow-up interview.

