#### Headache diary

A modified version of a validated headache diary 
[87,88] will be used in order to prospectively record data on headache frequency, headache intensity (VAS) and medication. We have also added self-reported number of sick-leave days. The completion of the diary for a two week period will be required at baseline, at three, six and twelve months for both BI and BAU patients. Written instructions for the completion of the diary will be mailed to the patients.

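### The 12-month relapse rate is counted in a group selected on one 3-month reading, so it overstates relapse and tilts any arm comparison towards BI

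*Protocol article*

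**What the plan says.** **Entry** (Recruitment, Patients). Invitation rests on one screening questionnaire: "All patients with 15 or more days with self-reported headache per month and headache medication utilization on 10 days or more per month".

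**3-month status** (Table 3). The row is "Difference between BI and BAU in proportion of cases without chronic headache and without medication overuse". The text under Outcome measures describes this kind of outcome as "Proportions fulfilling commonly used clinical definitions of chronic headache (≥15 days/month) and medication overuse". The headache line is therefore the entry line. No number of days is printed for medication overuse.

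**12-month relapse** (Table 3). The whole entry is "Relapse rate compared with status at 3 month", marked at 12 months only. The reference point is printed; the denominator, threshold and any confirmation rule are not.

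**Context.** The abstract names maintenance of improvement as a secondary outcome. The Statistics section says hypotheses on the secondary outcomes will be tested. The Discussion lists regression towards the mean among the reasons why control groups improve and relies on the parallel control arm. Ethics and data security allows BAU practices to receive the BI course, and so to deliver BI, if the 3-month result is significant.

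**The concern.** A patient can relapse only after having improved, so the 3-month reference point fixes the denominator: patients classed as improved at 3 months. Two consequences follow.

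- Randomisation does not protect the comparison. Membership of the group is itself an effect of treatment. BAU remitters are mainly patients who read low that month; BI remitters are a mixture of those and patients who truly improved.
- Selection on one low reading is followed by regression back. A patient admitted on a high reading, low at 3 months and high again at 12 months counts as a relapse although nothing changed.

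The parallel arm answers regression to the mean for the 3-month contrast. It does not answer it for a rate conditioned on 3-month status. At stake is the reading of durability: a higher relapse rate in BAU could be taken as evidence that the effect of BI lasts, and a sizeable rate in BI as evidence that it fades, with neither being true.

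**Working it through.** The article gives no expected remission rate, relapse rate or within-patient SD, so there is no stated figure to reproduce. The check asks what the relapse row shows when true relapse is zero.

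**1. Direction, by algebra.** Let *c* be the chance remission probability at 3 months in both arms, *t* the extra true remission in BI, and *b* the share of chance remitters back over the line at 12 months. True remitters never relapse.

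- Remission: BAU = c; BI = t + (1−t)c
- Apparent relapse: BAU = b; BI = (1−t)cb / [t + (1−t)c], which is below b whenever t > 0
- Sustained remission: BAU = c(1−b); BI = t + (1−t)c(1−b)

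With illustrative c = 0.20, t = 0.20, b = 0.70:

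- Remission: 0.20 + 0.80×0.20 = 36% in BI versus 20% in BAU, a difference of 16 points (diluted but valid)
- Relapse: 0.80×0.20×0.70 / 0.36 = 0.112/0.36 = 31% in BI versus 70% in BAU
- Sustained remission: 0.20 + 0.80×0.20×0.30 = 24.8% in BI versus 0.20×0.30 = 6.0% in BAU, a difference of 18.8 points

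The relapse gap of 39 points is produced wholly by the denominator.

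**2. Size, by simulation.** All of the following are assumptions except the entry cut-offs and the 15-day outcome line.

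- True monthly headache days on the GP list: exponential, mean 5, 8 or 12, capped at 30, plus 1% near-daily. Medication days = headache days × Beta(3,2).
- Each reading = truth + normal error with SD 2, 3 or 4 days, error correlation 0.6, rounded and limited to 0–30.
- Entry: one reading ≥15 headache and ≥10 medication days.
- BAU truth unchanged; BI truth permanently lowered by 4 headache and 6 medication days.
- Remission: <15 and <10 days. Relapse: either measure back at or over its cut-off at 12 months.

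| Mean, SD | Remission BAU / BI | Apparent relapse BAU / BI | Sustained BAU / BI |
|---|---|---|---|
| 5, 2 | 7.4 / 37.3% | 55.2 / 20.2% | 3.3 / 29.8% |
| 5, 3 | 14.9 / 41.6% | 48.8 / 22.3% | 7.7 / 32.4% |
| 5, 4 | 23.3 / 47.4% | 43.5 / 22.7% | 13.1 / 36.6% |
| 8, 2 | 4.9 / 28.4% | 59.2 / 23.9% | 2.0 / 21.6% |
| 8, 3 | 9.6 / 31.2% | 53.7 / 28.0% | 4.4 / 22.5% |
| 8, 4 | 14.9 / 35.1% | 49.8 / 29.2% | 7.5 / 24.9% |
| 12, 2 | 3.2 / 19.9% | 61.0 / 25.9% | 1.2 / 14.7% |
| 12, 3 | 6.2 / 22.0% | 56.3 / 31.2% | 2.7 / 15.2% |
| 12, 4 | 9.5 / 24.6% | 53.7 / 33.7% | 4.4 / 16.3% |

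BAU exceeds BI in all nine settings, with no true relapse in either arm.

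**3. Does it depend on details the article leaves open?** At mean 8, SD 3:

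- Headache cut-off alone: 43% versus 25%
- Outcome medication cut-off of 15 days: 44% versus 25%
- Both measures must return: 25% versus 8%

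The level changes; the direction does not.

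**4. A higher-burden population.** With normal true levels (headache mean 20, SD 6; medication mean 14, SD 7) and error SD 2–5, apparent relapse is about 77–81% with no effect and 41–62% after the permanent BI effect. Chance remission on both measures is only 0.5–3%.

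**5. Numbers of patients.** The plan has 160 patients, or 80 per arm. At mean 8, SD 3 the relapse row rests on 0.096×80 ≈ 8 BAU and 0.312×80 ≈ 25 BI remitters.

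**The case against.** The strongest reply is that the relapse rule is not printed, so the criticism is of an inferred rule, and that a condensed article may leave it to the full protocol. This stands for the threshold: relapse as a return over the entry cut-offs is an inference. It does not stand for the reference point, which is printed and from which the selection follows whatever threshold is later chosen (step 3).

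Several stronger readings are tempting and not supported:

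- *Both outcome cut-offs equal the entry cut-offs.* Only the headache line does. The 10-day medication cut-off used here is an assumption.
- *Nothing guards against a single low month.* Under Headache classification the authors "defined chronic headache as 15 or more headache days per month for at least 3 months and/or 180 or more headache days per year". Whether that duration element applies to the 3-month status row is not stated.
- *Stable patients become responders.* The improvement outcomes in Table 3 are reductions of more than 25% and 50%, not threshold crossings.
- *The 3-month status row is invalid.* It compares randomised arms; chance remission affects both and mainly dilutes the difference.
- *The trial cannot show whether BI lasts.* Other 12-month rows (headache days, medication days, percentage reductions, headache index, intensity) are taken from baseline and not conditioned on 3-month status.

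It is also fair that the relapse row, unlike the status row, is not labelled as a difference between arms, and that the follow-up year is described as open. The between-arm bias therefore arises only if the arms are compared. The overstatement of relapse within each arm arises regardless.

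**Conclusion.** The concern holds for the relapse row. Because it is conditional on 3-month status, it overstates relapse, and a comparison of arms on it favours BI with no true difference in durability. The direction needs only that BI produces some true remission and that part of 3-month remission is chance. The size cannot be derived from the article. Under the GP-list assumptions it is about 43–61% in BAU and 20–34% in BI with zero true relapse, and higher in a high-burden population. Even the GP-list settings are rough: the lowest mean screens in about 5% of the list, whereas the power section expects about 10 medication-overuse patients per 1000. These rates overlap the 20–60% that the Background cites from earlier studies, so agreement with those studies would not show that an observed rate is genuine relapse. The primary outcomes and the 3-month secondary comparisons are unaffected. This is a worthwhile improvement to one secondary outcome, not a threat to the trial.

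**What to change.** 1. In Table 3, add sustained remission as the maintenance outcome: the proportion of all randomised patients without chronic headache and without medication overuse at both 3 and 12 months, using the definitions of the 3-month status row. Compare the arms on this, handling missing status by the multiple imputation already planned.
2. Keep relapse among 3-month remitters as descriptive only, with the denominator given per arm and no between-arm test.
3. State that 12-month arm comparisons are subject to the possible BAU cross-over. This applies to sustained remission too, but with a limit: a BAU patient not in remission at 3 months cannot later count, so cross-over can act only through BAU patients already in remission by then.
4. Leave the 3-month status row as it is. An added 25% change margin is not worth requiring: at mean 8, SD 3 it lowers apparent relapse only from 54% to 45% in BAU and from 28% to 22% in BI.

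**Cost.** A few lines in Table 3 and the Statistics section. No new data are needed, since the 12-month telephone interview already covers headache days and medication use. The price is a less flattering durability figure: at mean 8, SD 3, BI would show 22.5% sustained remission, where the complement of its relapse rate would be 72%.
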